#### 2.3.3. Safety Endpoints

We will evaluate if sustained um-PEA treatment is well tolerated, with minimal side-effects. Incidence of adverse effects during the study period will be measured using the UKU side-effect rating scale [42].

### 2.4. Biological Measures

Blood tests for hematology (i.e., full blood count and hemoglobin), biochemistry (i.e., urea and electrolytes, liver function test, lipid profile), sex hormones quantification [i.e., follicle-stimulating hormone (FSH), luteinizing hormone (LH)], and hypothalamic-pituitary-adrenal axis activity-related indices quantification (i.e., morning cortisol at 8 a.m.) will be carried out at the clinical research recruitment hub as per their standard procedure. Cytokines and chemokines will be analysed on available serum samples using customized multiplex immunoenzymatic assays (Ella instrument, Bio-Techne, Minneapolis, MN, USA) to characterize the inflammatory profile. Serum samples will be collected for performing “metabolic fingerprinting” analysis using Surface-Enhanced Raman Scattering (SERS) spectroscopy, a rapid, label-free, and non-destructive method revealing molecular information about the biochemical composition of biofluids by analysing shifts in SERS spectral profiles [46,47,48]. Additionally, blood and fecal samples will be collected for the measurement of eCB mediators using liquid chromatography-mass spectrometry (LC/MS) techniques [49,50], and the determination of the microbial composition in feces using Next Generation Sequencing (NGS) of 16SRNA and shotgun metagenomics methodologies [51].

### 2.5. Study Setting and Participants

#### 2.5.1. Screening and Recruitment

The study will take place at the Unit of Psychiatry and Eating Disorders of the Udine University Hospital, a university clinical research facility in Italy. Help-seeking individuals presenting at the Unit of Psychiatry and Eating Disorders upon referral from General Practitioners (GPs) or other mental healthcare professionals from Udine catchment area and identified as CHR-APS patients by the clinical team will be considered for enrolment against inclusion and exclusion criteria. They will be involved into an internal pilot, that will progress to the open-label trial. Patients expressing an interest in participating to the study will be approached by study researchers and given a patient information sheet and consent form (https://osf.io/nrc5b, accessed on 5 December 2024).

Those who agree to take part in the study will be invited for a screening visit.

#### 2.5.2. Inclusion Criteria

The following are the participants’ inclusion criteria:Individuals diagnosed with CHR-APS, as defined using CAARMS criteria [1];Aged 18–35 years;To be able to understand and communicate in Italian;To be able to give informed consent.

#### 2.5.3. Exclusion Criteria

The following are the participants’ exclusion criteria:Lifetime history of a psychotic or manic episode lasting 7 days or longer;Active suicidal ideation indicating significant current risk or history of serious suicide attempt in the opinion of the Principal Investigator (PI), as evaluated at the screening stage;Lifetime neurological disorders (e.g., epilepsy, except febrile convulsions) or severe intercurrent physical illness;Current treatment with psychotropic medication, with the exception of Selective Serotonin Reuptake Inhibitor (SSRI) stable monotherapy (at least 8 months);Lifetime treatment with antipsychotic medication for more than 7 days;Intelligence quotient (IQ) < 70;Female patients who are pregnant, lactating or not using an acceptable effective form contraception if they are at risk of becoming pregnant;Taking part in another pharmacological trial.

#### 2.5.4. Demographics

At the time of the screening visit, socio-demographic and clinical characteristics of each participant will be recorded in the trial CRFs (https://osf.io/2vayh, accessed on 5 December, 2024), including (i) age, (ii) sex, (iii) height, (iv) weight, (v) body mass index (BMI), (vi) reason for first referral, (vii) housing situation, (viii) marital status, (ix) nationality, (x) level of education, (xi) working situation, (xii) handedness, (xiii) prior contact with child & adolescent mental health service (CAMHS), (xiv) prior contact with adult mental health service (AMHS), (xv) predating hospitalizations for mental health issues, (xvi) predating contact with social services, (xvii) predating diagnosis, (xviii) age at predating diagnosis, (xix) comorbid neurodevelopmental disorders (NDDs), (xx) comorbid physical illnesses, (xxi) impairment in daily autonomies, (xxii) intellectual disability, (xxiii) brain magnetic resonance imaging (MRI), (xxiv) childhood adversities (CAs; i.e., sexual/physical/psychological/ emotional abuse, physical/emotional neglect, exploitation, peer victimization/bullying), (xxv) any CAs, (xxvi) recent stressful life events (SLEs), (xxvii) predating treatment with any psychotropic medications, (xxviii) type of predating medication, (xxix) current treatment with any psychiatric medications, (xxx) type of current medication, (xxxi) lifetime addicting substance use (any), (xxxii) current addicting substance use (any), (xxxiii) lifetime cannabis use, (xxxiv) current cannabis use, (xxxv) lifetime alcohol use, (xxxvi) current alcohol use, (xxxvii) lifetime stimulant use, (xxxviii) current stimulant use, (xxxix) NDDs family history, (xl) major mental health disorders (MMHDs) family history, (xli) substance use disorders (SUDs) family history, (xlii) suicide/suicide attempt family history, (xliii) neurological disorders family history.

Substance use information will be collected as screening measures, using dedicated interviews [37,38,39,40].

### 2.6. Intervention

Participants will initially undertake a 12-week daily treatment with oral um-PEA 600 mg in tablet form (Normast^®^). During the 24-week extension phase of the study, the trial medication will be taken from once a day up to twice a day (600–1200 mg per day), based on clinical judgment of the improvement obtained at that point, around mealtime. Being a food supplement/nutraceutical, um-PEA can be purchased at pharmacies without a medical prescription [52]. While unknown risks cannot be excluded, serious adverse events including overdose have not been documented [53,54]. Um-PEA will be obtained by a pharmaceutical company operating under good manufacturing practice conditions with appropriate certification.

The information presented on the labels for um-PEA will comply with applicable national and local regulations. Only qualified physicians clearly given this role by the PI will prescribe the study medication on the study delegation log. Only people designated by the PI will collect medication. Only um-PEA supplied for this study will be dispensed against the study specific prescription. Full accountability records will be completed including recording the batch, expiry date, people dispensing/checking the prescription, quantity and date of drug returns, empty packaging. Nothing will be destroyed without the authorization from the PI.

Um-PEA will be stored at room temperature (<25 °C) and not kept in a refrigerator, in compliance with local regulations. It will be stored in a secure area away from other treatments and clearly marked for this study.

### 2.7. Data Management and Confidentiality

Study-related information will be stored securely at the study site. All participants’ information will be stored in locked file cabinets in areas with limited access. All laboratory specimens, reports, data collection, process and administrative forms, will be identified by a coded identification (ID) number only to maintain participant confidentiality and stored separately from records containing names or other personal identifiers. Local databases will be secured with password-protected access systems. Forms, lists, logbooks, appointment books, and any other listings that link participant ID numbers to other identifying information will be stored in a separate, locked file in an area with limited access. Participants’ study information will not be released outside of the study without the written permission of the participant.

### 2.8. Statistical Methods

#### 2.8.1. Data Verification, Statistical Monitoring, and Analysis

At the study start, a structured data verification plan will be agreed and developed by the Head Statistician ([name]) of the research team. Quality of data will be routinely checked in terms of consistency across paper- and electronic-based entry systems. Statistical monitoring will include patient severity level, eventual withdrawals, baseline data, FUP visits data, and adverse effects. The research team will approve a Statistical Analysis Plan within the early stages of the study, and before the Head Statistician summarizes any data (i.e., with univariate and repeated measures analysis, including preliminary assessment and management of any outliers and assessment of the metric qualities of measurements, such as normality and sphericity, where necessary). Proportions will be presented for each feasibility outcome. Interim analyses are not planned. The Head Statistician will both carry out and interpret statistical analysis. Our primary analysis will involve a generalized linear model with CAARMS psychotic symptom severity as the dependent measure and time as a repeated measure (possibly supplemented with analyses at the participant level, as random effects in mixed models). We are interested in whether there is a significant benefit over time with um-PEA treatment: therefore, particular interest will be placed on time as a fixed factor on the severity of outcomes. CAARMS distress and total score as well as HADS and GF ratings will be analysed in a similar manner. We will also conduct paired tests (both parametric and non-parametric) based on baseline and endpoint assessments to examine measures of CAARMS severity, CAARMS frequency/duration, and secondary outcomes. Trend and rates of adverse effects will be reported, as well as reasons for dropouts from the trial.

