### 2.2. Sample Size Calculation

The primary analysis (see below) will focus on total severity of APS as evaluated using the Comprehensive Assessment of At-Risk Mental State (CAARMS) [1], measured in three longitudinal assessments (i.e., Feasibility phase: Baseline, T1, and T2). Accepting a type-I error (α) of 5% and a type-II error (β) of 20%, we would need a sample of 8–12 participants to detect an effect of large size (partial-η2 ≥ 0.140). This value was obtained considering a moderate-to-large test-retest reliability of measurements over time (+0.500 < r ≤ +0.700) and the absence of correction for sphericity. With an intermediate sphericity correction (ε = 0.750), the required sample size would be 10–14; in the worst case (ε = 0.500), instead, 12–19 participants would be needed. We therefore propose the recruitment of 20 participants, considered coherent with a pilot study and sufficient to evaluate feasibility outcomes of clinically significant size, also considering a low drop-out rate (i.e., ≤ 20%). When large statistically significant results are obtained on total severity of APS, specific APS severities will be further investigated (i.e., considering four P1 scales). For this secondary endpoint, on average, a sample-size of 17 participants would be sufficient to detect large effects, also considering Bonferroni’s correction for multiple independent comparisons (i.e., α = 0.012). Power analyses were carried out with G*Power-3.1.9.7 [45].

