#### 2.8.2. Missing Data

We expect withdrawn patients to be missing at random, and very few participants withdrawing consent. All patients having at least one post-baseline outcome measure will be included in each analysis. Nonetheless, patterns of missing data will be explored to investigate any evidence against missing at random, whose impact on the analysis will be considered by introducing imputation methods (i.e., Multiple Imputation or MissForest approach, depending on the missing data type).

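### The primary analysis, as powered, is an overall three-visit test of time with no named 12-week contrast, and the inclusion promise in 2.8.2 does not fit the paired tests

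*Protocol article*

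**What the plan says.** Section 2.8.1 designates one primary analysis: "Our primary analysis will involve a generalized linear model with CAARMS psychotic symptom severity as the dependent measure and time as a repeated measure". A mixed model with participant-level random effects is offered only as a possible supplement. The stated interest is in a benefit over time, and the term to be examined is time as a fixed factor. The same paragraph adds: "We will also conduct paired tests (both parametric and non-parametric) based on baseline and endpoint assessments". These paired tests cover CAARMS severity, frequency/duration and the secondary outcomes.

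Section 2.2 shows which test the authors had in mind. The calculation rests on partial eta-squared of at least 0.14, three assessments (baseline, T1 at 4 weeks, T2 at 12 weeks), between-visit correlations of 0.5 to 0.7, 5% type I error, 80% power and a range of sphericity corrections, for example: "With an intermediate sphericity correction (ε = 0.750), the required sample size would be 10–14".

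Section 2.3.2 says that endpoints of the 12-week trial are assessed by comparing follow-up visits with baseline. It does not say which visit decides.

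Section 2.8.2 states: "All patients having at least one post-baseline outcome measure will be included in each analysis". It mentions imputation (Multiple Imputation or MissForest) in connection with evidence against missing at random.

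**The concern.** An overall test of a three-level time factor answers whether the three visit means are all equal. It has 2 degrees of freedom before sphericity correction, no direction and no decisive visit. The treatment phase runs 12 weeks, and a reader will take a positive primary result as evidence of improvement at its end. The overall test does not establish that, because a transient change at T1 is enough to make it significant. The result also has a consequence within the plan: under 2.2, a large significant result on total severity opens the testing of the four P1 scales.

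The second strand is the analysis set. A paired baseline-to-endpoint test needs a T2 value. Section 2.9 describes one way in which participants with T1 but no T2 can arise: those who progress to psychosis leave the intervention and are then assessed only for safety. Unless values are imputed, such participants cannot be in each analysis as 2.8.2 promises.

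**Working it through.** **Step 1. Which test does 2.2 power?** Inputs from 2.2: α = 0.05, power 0.80, partial η² = 0.14, m = 3 visits, r from 0.5 to 0.7, ε = 1, 0.75 or 0.50.

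- f² = 0.14 / 0.86 = 0.1628.
- Noncentrality λ = f² · N · m · ε / (1 − r); df1 = (m − 1)ε; df2 = (N − 1)(m − 1)ε.
- Example: N = 12, r = 0.5, ε = 1 gives λ = 0.1628 × 12 × 3 / 0.5 = 11.72 on 2 and 22 df, power 0.82. N = 11 gives 0.78, so 12 is the smallest sufficient N.

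| ε | N at r = 0.5 | N at r = 0.7 | Stated in 2.2 |
|---|---|---|---|
| 1 | 12 | 8 | 8–12 |
| 0.75 | 14 | 10 | 10–14 |
| 0.50 | 19 | 12 | 12–19 |

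All three ranges reproduce. The alternative effect-size convention (λ = f² · df2) gives 33, 39 and 52 and does not match. The test that the protocol has powered is the overall repeated-measures F test of time.

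**Step 2. Can that test be significant with nothing changed at T2?** Assumptions, not in the documents: normal data, SD 1, equal correlations, r = 0.6, visit means (0, −0.8, 0).

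- Grand mean −0.2667. Variance of the means = (2 × 0.2667² + 0.5333²) / 3 = 0.1422.
- N = 20: λ = 20 × 3 × 0.1422 / 0.4 = 21.3 on 2 and 38 df, power 0.984. Simulation with 6,000 replicates gave 0.982.
- The T2-minus-baseline contrast has true value 0 and rejects at its nominal 5% (0.046 simulated).
- Over the protocol's own range of r, the overall test is significant in 95% (r = 0.5) to 99.8% (r = 0.7) of trials.

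**Step 3. What does a single T2 contrast cost or gain in power?** Take 16 participants with T2 data (20 less the 20% drop-out ceiling in 2.2), r = 0.6 and a true fall of 0.8 SD at T2. For the contrast, the SD of the difference is √(2 × 0.4) = 0.894, so the noncentrality is (0.8 / 0.894) × √16 = 3.58 on 15 df, and power is 0.92 whatever happens at T1.

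| Visit means | Overall F test | T2 − baseline |
|---|---|---|
| (0, −0.4, −0.8), linear | 0.87 | 0.92 |
| (0, −0.6, −0.8), mostly early | 0.90 | 0.92 |
| (0, −0.8, −0.8), early and maintained | 0.95 | 0.92 |

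The differences are small, and their sign depends on the time course.

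**Step 4. Who can enter which analysis?** Consider a participant with baseline and T1 but no T2.

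| Analysis | Usable without imputation? |
|---|---|
| Paired tests, baseline to endpoint | No |
| Repeated-measures ANOVA on complete cases | No |
| Generalized linear model fitted by GEE | Yes |
| Mixed model (optional in 2.8.1) | Yes |

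At the drop-out ceiling in 2.2, up to 0.20 × 20 = 4 participants could be affected.

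**The case against.** Several stronger readings are tempting, and the documents do not support them.

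- *Three competing tests inflate the error rate.* With no true change, at least one of the F, paired t and Wilcoxon tests is significant in about 8% of simulated trials. That would matter only if any of the three could be read as the primary result. Section 2.8.1 labels one analysis primary and introduces the paired tests as additional, so 8% is not the plan's error rate.
- *Participants with only T1 cannot be included, and their data are discarded.* This goes too far. The named model could be fitted by GEE, the mixed model is permitted, and 2.8.2 names imputation. Section 2.9 says that data already collected are retained in the final analysis, and that those who only stop treatment continue with follow-up visits. What stands is that the named model does not guarantee the promised set, and that the paired tests conflict with it unless values are imputed.
- *The overall test is worse because it also rejects for worsening.* A two-sided contrast does so too. In both cases direction is read from the estimates.
- *The contrast is more powerful.* Not in general: step 3 shows the order reversing for an early maintained response.

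It is also fair to say that the protocol speaks of benefit over time and of follow-up visits in the plural, so that a three-visit test is consistent with both its wording and its sample size. The planned paired tests would expose a dip that had reversed. The contrast, covariance structure and degrees of freedom are ordinary analysis-plan content, that plan is not shown, and this is an open-label pilot. These arguments temper the point but do not remove it: the protocol itself has fixed and powered a primary test that does not show whether patients are better at 12 weeks.

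**Conclusion.** The point holds in a limited form. The primary analysis, as powered, is an overall test of time that can be significant in about 98% of trials with no change at 12 weeks. This figure rests on a constructed pattern (0.8 SD dip at T1, full reversal by T2, n = 20, r = 0.6, normal data). It shows what the test can do and does not predict this trial. No visit contrast is named as the primary result. The inclusion promise in 2.8.2 cannot hold for the paired tests in participants without T2 unless values are imputed. Whether it holds for the primary model depends on how that model is fitted, which the protocol leaves open. This is a worthwhile and inexpensive improvement; it does not show that the sample size is wrong or that the planned error rate is breached.

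**What to change.** 1. In 2.8.1, make a mixed model for repeated measures the primary analysis, with visit as a factor and small-sample degrees of freedom. Name the T2-minus-baseline estimate with its 95% CI as the single primary result.
2. State explicitly that the overall time test, the T1 contrast and the paired tests are supportive.
3. Align 2.8.2 with that model, and limit its inclusion promise for the paired tests to participants with an observed or imputed T2 value.

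The cost is wording in the protocol and the analysis plan, which 2.8.1 says will be approved before any data are summarised. No new data are needed. There are two downsides. A benefit seen only at T1 would no longer count as primary success. If the response is early and maintained, the contrast has slightly less power than the overall test (about 92% against 95% with 16 participants, under the assumptions of step 3).

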#### 2.8.2. Missing Data

We expect withdrawn patients to be missing at random, and very few participants withdrawing consent. All patients having at least one post-baseline outcome measure will be included in each analysis. Nonetheless, patterns of missing data will be explored to investigate any evidence against missing at random, whose impact on the analysis will be considered by introducing imputation methods (i.e., Multiple Imputation or MissForest approach, depending on the missing data type).

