### 2.9. Withdrawal of Participants

In accordance with the Declaration of Helsinki [55], all participants have the right to withdraw from the study at any time, without the need to provide a reason, and without affecting their future medical care. Participants will be informed of this right prior to giving consent. If a participant decides to withdraw, it will be clarified that they are only discontinuing the study treatment while continuing follow-up visits. Should a participant wish to fully withdraw from the study, their decision will be respected. Efforts will be made to determine the reason for withdrawal, although participants are not required to provide any explanation. Data already collected will be retained and included in the final analysis. The PI may also withdraw participants for various reasons, including but not limited to protocol violations, intercurrent illness, adverse events, serious adverse events, suspected unexpected serious adverse reactions, administrative reasons, or if participation in the trial interferes with ongoing care or results in symptomatic worsening.

In these cases, participants will continue to be followed up with the same schedule of research assessments as those who remain in the study, until they complete the 12-week follow-up period or until they develop frank psychosis, whichever occurs first. Participants who experience progression to first-episode psychosis will exit the study intervention, be classified as treatment failure, and only be assessed for safety outcomes until completing the 12-week follow-up period.

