## Figures and Tables

**Table 1 brainsci-14-01230-t001:** Study flowchart.

Procedures	Screening Phase	Feasibility Phase			Extension Phase	
	Screening (Day-7)	Baseline (Day 0)	T1 (4 weeks ± 7 Days)	T2 (12 Weeks ± 14 Days)	T3 (24 Weeks ± 14 Days)	T4 (36 Weeks ± 14 Days)
Informed consent	X					
Medical history	X					
Physical examination	X	X		X		X
Electrocardiogram	X	X		X		X
Urinalysis	X			X		X
*AUDIT* [37], *FTND* [38], *SDS* [39], *CEQ* [40]	X					
*TFLB* [41]		X	X	X	X	
Pregnancy test	X	X	X	X	X	
Hematology, biochemistry	X			X		X
Concomitant medication	X	X	X	X	X	X
Exclusion criteria	X	X				
Intelligence quotient	X					
*UKU-SERS* [42]		X	X	X	X	X
*Um-PEA* dispensing		X	X	X	X	
Compliance assessment			X	X	X	X
*CAARMS* [1]	X	X	X	X	X	X
*HADS* [43], *GF* Social/Role scales [44]		X	X	X	X	X
Microbiome, inflammation, eCBome blood and stool assessments		X	X	X	X	X

*AUDIT*, Alcohol Use Disorders Identification Test; *FTND*, The Fagerstorm Test for Nicotine Dependence; *SDS*, Severity of Dependence Scale; *CEQ*, Cannabis Experience Questionnaire; *TFLB*, The Timeline Followback; *UKU-SERS*, UKU Side Effect Rating Scale; *Um-PEA*, Ultramicronized-Palmitoylethanolamide; *CAARMS*, The Comprehensive Assessment of At-Risk Mental State; *HADS*, Hospital Anxiety and Depression Scale; *GF*, Global Functioning.

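### The one-post-baseline-measure rule has no exception for safety, so a treated participant fully lost before week 4 would drop out of the adverse-effect rate

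*Protocol article*

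**What the plan says.** **Inclusion rule.** Section 2.8.2 states: "All patients having at least one post-baseline outcome measure will be included in each analysis". No analysis is exempted.

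**Safety endpoint.** Section 2.3.3 names one instrument: "Incidence of adverse effects during the study period will be measured using the UKU side-effect rating scale". Section 2.8.1 adds: "Trend and rates of adverse effects will be reported, as well as reasons for dropouts from the trial". Neither section gives a denominator for the rates.

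**Timing.** Section 2.6 says: "Participants will initially undertake a 12-week daily treatment with oral um-PEA 600 mg in tablet form". Table 1 shows the first dispensing at Baseline (Day 0). The next column is "T1 (4 weeks ± 7 Days"), and no visit is scheduled in between.

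**Leaving the trial.** Section 2.9 separates three routes:
- A participant who decides to withdraw is first told what this means: "it will be clarified that they are only discontinuing the study treatment while continuing follow-up visits".
- After withdrawal by the PI, for which adverse events are a listed reason, "participants will continue to be followed up with the same schedule of research assessments as those who remain in the study". This lasts to week 12 or frank psychosis.
- Complete exit is also possible: "Should a participant wish to fully withdraw from the study, their decision will be respected".

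The same section says that data gathered before withdrawal are kept and used in the final analysis.

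**The concern.** A requirement for a post-baseline measure is common in analyses of change in a score, because someone with only a baseline value shows no change. It suits an adverse-effect rate poorly. There the natural denominator is everyone exposed, and an early exit may itself be the result of intolerance.

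Here the earliest qualifying measure comes after about three to five weeks of exposure. A person who takes um-PEA, feels unwell and leaves the study altogether in that window would be missing from both the numerator and the denominator. Safety and tolerability is one of the three stated purposes in section 2.1. With 20 participants and no control arm, each person is 1/20 = 5 percentage points.

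**Working it through.** The article states no adverse-effect rate and no safety denominator, so there is no figure of the plan's own to reproduce on this point.

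**Inputs from the protocol article**
- Participants: 20, single arm (section 2.2).
- Planned dropout: at most 20%, so up to 0.20 × 20 = 4 (section 2.2). Timing and cause are not given.
- First post-baseline UKU: day 28 ± 7, so day 21 to day 35 (Table 1).

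**Assumed inputs (the article gives none)**
- k = treated participants with no post-baseline measure.
- a = those of the k who had an adverse effect.
- x = participants with an adverse effect among the remaining 20 − k.

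**Who can fall into k?** Setting section 2.9 beside Table 1:

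| Route before T1 | T1 assessment kept? | Affected by the rule? |
|---|---|---|
| Stops treatment only | Yes | No |
| Withdrawn by the PI | Yes | No |
| Progresses to psychosis | Yes, for safety | No |
| Withdraws fully, or is lost to follow-up | No | Yes |

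**Formulas**
- All treated: (x + a)/20.
- Under the rule: x/(20 − k).
- The rule lowers the rate when x/(20 − k) < (x + a)/20. This rearranges to a/k > x/(20 − k): adverse effects must be more frequent among those excluded than among those kept.

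**Results**

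| k | a | x | All treated | Under the rule | Difference (points) |
|---|---|---|---|---|---|
| 1 | 1 | 2 | 3/20 = 15.0% | 2/19 = 10.5% | −4.5 |
| 1 | 1 | 4 | 5/20 = 25.0% | 4/19 = 21.1% | −3.9 |
| 2 | 2 | 2 | 4/20 = 20.0% | 2/18 = 11.1% | −8.9 |
| 4 | 4 | 2 | 6/20 = 30.0% | 2/16 = 12.5% | −17.5 |
| 4 | 1 | 4 | 5/20 = 25.0% | 4/16 = 25.0% | 0.0 |
| 1 | 0 | 2 | 2/20 = 10.0% | 2/19 = 10.5% | +0.5 |
| 4 | 0 | 4 | 4/20 = 20.0% | 4/16 = 25.0% | +5.0 |

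When every excluded person had an adverse effect, each one costs about 4 to 4.5 points. The rows with k = 4 are the outer limit, because they place all the planned dropout before T1 and make all of it complete exit.

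**The case against.** **The rule may be meant for efficacy only.** It stands under Missing Data, next to text on missingness and imputation, and speaks of an outcome measure. It says who is included and does not expressly exclude anyone else. That reading is plausible. The sentence nevertheless covers every analysis without qualification, and one clause would settle it.

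**Analysis sets are usually left to the SAP.** This is true, and the absence of a named safety population is no error in itself. The point rests on a rule that the article does state.

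**Few people will be affected.** Section 2.8.2 expects very few to withdraw consent, and section 2.9 keeps most leavers under assessment. This stands, and it limits the size of the problem.

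**Dropout reasons are reported anyway.** They are, but separately from the rate, and participants need not give one.

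Three stronger readings are tempting, and the document does not support them:
- *Everyone who leaves before week 4 is removed.* Section 2.9 keeps those who only stop treatment, and those whom the PI withdraws for adverse events, on the schedule.
- *The bias always favours um-PEA.* The direction depends on why the excluded people left. Excluding people without adverse effects raises the rate.
- *The rule could turn a failed 80% completion criterion into a pass.* For example, 15/20 = 75% would become 15/18 = 83% if two of five dropouts were removed. Sections 2.1 and 2.3.1 already express completion as a proportion of participants, and leaving early is itself the non-completion event. A missing-data rule does not naturally redefine that denominator.

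**Conclusion.** The point holds in a narrow form. As written, section 2.8.2 takes a treated participant who fully withdraws or is lost before T1 out of the adverse-effect rate. It also sits uneasily with the statement in section 2.9 that data already gathered enter the final analysis, and the two sections should be reconciled.

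The size depends on assumed counts. With 20 treated and 2 to 4 adverse effects among those kept, each excluded person with an adverse effect lowers the rate by about 4 to 4.5 points. The bias is downward only if adverse effects are more frequent among the excluded than among the kept. It can also be zero, or upward by as much as 5.0 points in the cases worked here.

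The rule should be changed because one person matters at this sample size and the remedy is cheap. The document gives no evidence that such exits will be common.

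**What to change.** In section 2.8.2, with the SAP worded to match:
1. Limit the requirement for a post-baseline measure to the CAARMS, HADS and GF outcome analyses.
2. Report adverse effects in all participants who took at least one dose of um-PEA. Count those recorded outside scheduled UKU visits or given as the reason for withdrawal.
3. For clarity, confirm that 12-week completion uses all enrolled participants as the denominator, as sections 2.1 and 2.3.1 imply.

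This costs a few sentences and needs no new visits. The reported adverse-effect rate may look slightly less favourable. The new denominator cannot recover an adverse effect that nobody recorded, so the number of treated participants without a post-baseline UKU should be given beside the rate.
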